#### **3.2. Intentionally Blank**

### 3.3. Sample Size Considerations

The LIFE trial has targeted the recruitment of **1600 participants** across 8 Field Centers.

The **primary aim** of the LIFE Study is to assess the long-term (average 2.7 yrs) relative effect of randomization of sedentary persons aged 70 to 89 years to a physical activity intervention on the **primary outcome** of time until major mobility disability defined as inability to walk 400 m.

The primary study hypothesis of LIFE will be tested based on a two-tailed significance level of 0.05. In this analysis, the "intention to treat" approach will be used in which participants are grouped according to randomization assignment.

The main comparisons of intervention groups with respect to the distribution of time until the first post-randomization occurrence of a primary outcome will be based on survival analyses. To compare intervention arms, we will use a likelihood ratio test from a Cox regression model, stratified by field center and gender. Failure time is measured from the time of randomization.

**Incidence of the Primary Outcome:** In the LIFE Pilot study (LIFE-P), after exclusion of LIFE-P participants reporting >125 min of moderate level exercise at baseline, we estimated the 1-year failure rate in the SA arm to be 18% (Kaplan-Meier estimate). LIFE-P was not designed to estimate whether this rate increases in future years of follow-up. However, from Health ABC data we project the annual incidence rate may increase by as much as 29% in years 2-4 in participants with characteristics similar to LIFE. Using this, we have conservatively incorporated a 15% increase in the average annual incidence rate in power calculations. Thus, we adopt assumptions of an initial annual incidence rate of **18%** and project that this rate will increase, on average, to **21%** after two years of follow-up.

**Effect Size:** We have calculated the power for effect sizes ranging from 20% to 25% relative effects. While too small to estimate a relative effective size with precision, LIFE-P observed a 29% (hazard ratio=0.71; 95% CI [0.44,1.20]) relative reduction in this primary outcome. A sensitivity analysis described below was performed to examine how varying levels in the rates of drop-ins, drop-outs, and non-adherence affect our relative effect sizes.

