**Average Follow-up:** We assume that recruitment will take 21 months. Power is calculated under two scenarios: 1) an assumption of a uniform recruitment rate; and 2) that the recruitment rate will accelerate during these 21 months so that approximately **50%** of participants will be recruited in the first 12 months, and **50%** will be recruited in the final **9** months. Close-out visits will occur for 3 consecutive months. The first participant recruited will have a close-out visit at 42 months (3.5 years) of follow-up and the final randomized participant will be followed for 23 months (1.9 years). Using these projected recruitment rates and lengths of follow-up, the average follow-up time will be approximately 31 months.

**Observational Follow-up:** Following the completion of the study intervention period, all participants will be asked to complete an additional assessment visit approximately one year after their last assessment visit to gather additional safety data and confirm the occurrence of the persistent mobility disability outcome. This visit will be referred as the Post Intervention Visit (PIV).

**Loss to Follow-up:** In LIFE-P, 400 m walk results or definitive adjudications were obtained in 94% (6 months) and 92% (12 months) of participants. We will assume that **loss to follow-up** accumulates at **8%/yr** throughout LIFE and factor this into all projections of power below. If loss to follow-up accrues at 7%/yr or 9%/yr rather than 8%/yr, the power for detecting the specified effect sizes would be increased or decreased by only 1%.

**Inference:** Our projections are based on a log-rank test with **2-sided significance level 0.05**. We have not adjusted this for interim analyses; however, the approach we recommend (Chapter 9) will not alter the final critical value materially.

**Calculations:** We have used SAS Proc Power, to allow incorporation of the increase in event rates during follow-up years 2-3.7 into our power calculations. In using this procedure, we assumed a uniform recruitment rate over 21 months. We have used the simulation option of NQuery Advisor to allow for calculation of power assuming recruitment of 50% of participants in the final 9 months of the 21 month recruitment period.

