Calculations were similar as for CVD event power. Because of the lower expected event rates (even with larger assumed effect sizes), the power is considerably lower. Power for ventilatory capacity is presented in Table

3.3.6. For simplicity and to be conservative, we have assumed an analysis of covariance model with adjustment for baseline but have not accounted for multiple follow-up measurements. A mixed model will ultimately be used to account for this correlation. Assumed standard deviations were 0.57 for FEV1 and 0.66 for FVC. With effect sizes of 0.05 units, there is modest power, but effect sizes of 0.1 there is substantial power. Power for sleep wake disturbances are presented in Table 3.3.7. As above, we assume 8%/year loss to follow-up. With a 5%/year event rate and a 30% effect (hazard ratio of 0.7), we would have 59% power to detect an effect using a two-sided test at the 5% level.

| Table 3.3.4. CVD Event Power |                         |                         |                         |
|------------------------------|-------------------------|-------------------------|-------------------------|
| Effect Size                  | 2%/yr SA Incidence Rate | 4%/yr SA Incidence Rate | 6%/yr SA Incidence Rate |
| 30%                          | 29%                     | 51%                     | 67%                     |
| 40%                          | 49%                     | 78%                     | 91%                     |
| 50%                          | 70%                     | 94%                     | 99%                     |

| Table 3.3.5. Hospitalized Pulm Event Power |                           |                           |                         |
|--------------------------------------------|---------------------------|---------------------------|-------------------------|
| Effect Size                                | 0.1%/yr SA Incidence Rate | 0.5%/yr SA Incidence Rate | 1%/yr SA Incidence Rate |
| 40%                                        | 7%                        | 16%                       | 28%                     |
| 50%                                        | 9%                        | 24%                       | 42%                     |
| 60%                                        | 11%                       | 34%                       | 59%                     |

| Table 3.3.6 Ventilatory Capacity Power |             |      |     |

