#### **6.2.16. Sleep-Wake Disturbances**

As a tertiary outcome, Sleep-Wake Disturbances will be evaluated with four validated instruments: Epworth Sleepiness Scale (ESS), which assesses perceived daytime drowsiness during several different activities, Insomnia Severity Index (ISI), which assesses insomnia symptoms, Pittsburgh Sleep Quality Index (PSQI), which assesses perceived sleep quality and disturbances, and Berlin Questionnaire (BQ), which assesses the clinical risk for obstructive sleep apnea. In addition to these instruments, two additional questions will be administered regarding napping behavior and the use of caffeine and energy drinks. These sleep instruments and the additional two questions will be completed at SV2 and at the 6, 18 and 30 month clinic visits.

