### **6.4.2. Randomization Algorithm**

Each eligible participant is randomized to one of the two arms of the clinical trial (physical activity intervention or successful aging program intervention) according to a variable block-length algorithm that is controlled by the Data Management, Analysis and Quality Control Center. This approach provides a high probability of balance between intervention assignments and makes anticipation of assignments difficult. Randomization

is stratified by field center to ensure nearly equal sample sizes for the two intervention groups within each center. This is necessary because the cohorts assembled by the centers differ due to local population characteristics and recruitment plans. Randomization is also stratified on gender to ensure nearly equal sample sizes for the two intervention groups within gender. Randomization assignment is made using a web-based randomization system that is part of the study data management system.

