**Tertiary aim #2** will be to explore the effects of the intervention on composite measure of the cognitive assessment battery. We will also construct a composite measure to include all components of the Cognitive Assessment Battery (but not the 3MSE, which is used as to screen participants for MCI/D classification). For this composite measure of cognitive performance we will z-transform each score by dividing its difference from the baseline mean by the baseline standard deviation, and then will average the z-transformed measures. This approach, rather than adopting weighted averages, provides slightly greater emphasis on executive function.] The relative effect of the PA intervention on this composite will be assessed with analyses of covariance applied to the measures collected at Year 2, with the baseline composite included as a covariate. Differences between intervention arms for each individual test that contributes to the composite measure will be described. A similar approach will be used to assess the impact of the intervention on executive functions using a composite score for the three executive function tests (Flanker, N-back and Task Switching)

**Tertiary aim #3** will be to assess the effects of the interventions on the SPPB score and 400 m walk speed within ethnicity/race, gender and baseline physical performance subgroups. Repeated measures analysis of covariance techniques for continuous outcomes (such as described for ADLs) will be used to explore these effects (mixed effects models). Estimates of the intervention effect will be obtained within these subgroups and formal tests of interactions between intervention and subgroup variables will be performed. Forest plots will be used to graphically display the results of these subgroup analyses.

**Tertiary Aims #4** will be assessed using a Cox proportional hazards model, stratified by Field Center and gender. Failure time is measured from the time of randomization to the first sleep-wake disturbance.

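### The sleep-wake power in Table 3.3.7 (59% in the quoted case) assumes roughly the full trial follow-up, but the instruments are given only to month 30, and only to month 18 for about a third of participants; power there is about 52%.

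*Protocol*

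**What the plan says.** Section 3.3 gives power for sleep-wake disturbance in Table 3.3.7, for control-arm rates of 3, 5 and 7% per year and effects of 20, 30 and 40%, with 8% loss per year. The text picks out one cell: "With a 5%/year event rate and a 30% effect (hazard ratio of 0.7), we would have 59% power to detect an effect". No observation period is given for this table.

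The analysis in Section 12.2 is a Cox model: "Failure time is measured from the time of randomization to the first sleep-wake disturbance".

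The outcome comes from four questionnaires. Section 6.2.16 says: "These sleep instruments and the additional two questions will be completed at SV2 and at the 6, 18 and 30 month clinic visits". The sleep row of Table 10.1 agrees, with no entry at months 12, 24, 36 or 42, at close-out or at the post-intervention visit. The table's mark for collecting a missed or old measure at close-out is on the ECG, ankle-brachial index and claudication rows, not on the sleep row.

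On trial follow-up, Section 3.3 has the first participant closing out at 42 months, while "the final randomized participant will be followed for 23 months (1.9 years".

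**The concern.** An onset can enter this analysis only if a later sleep assessment detects it. A participant whose follow-up ends before the month-30 visit has no sleep assessment after month 18, and no participant has one after month 30. If the power calculation credits everyone with observation up to the end of follow-up, it counts events that the schedule cannot observe. The printed power would then be too high, and a null sleep-wake result would be read against the wrong yardstick.

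**Working it through.** **Inputs.** Sample size: "The LIFE trial has targeted the recruitment of 1600 participants across 8 Field Centers" (Section 3.3). Allocation is 1:1, since randomization aims at "nearly equal sample sizes for the two intervention groups within each center" (Section 6.4.2), so 800 per arm. Two-sided 0.05, loss 8%/yr, uniform recruitment (Section 3.3). Follow-up 23 to 42 months. Sleep assessments at months 6, 18 and 30.

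**Formulas.** Annual risks become hazards by h = -ln(1 - p). For the quoted cell the control hazard is -ln(0.95) = 0.0513, the intervention hazard is 0.7 × 0.0513 = 0.0359, and the loss hazard is l = -ln(0.92) = 0.0834. The probability of an observed event by time T is h/(h + l) × [1 - exp(-(h + l)T)]. With D expected events:
- Schoenfeld: power = Φ(|ln HR| × √D / 2 - 1.96)
- Freedman: power = Φ((1 - HR)/(1 + HR) × √D - 1.96)
- The Lakatos log-rank method was run as a third check.

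**Step 1: reproduce the printed figure.** With follow-up uniform on 23 to 42 months, event probabilities are 0.1159 and 0.0828, so D = 800 × 0.1987 = 159.
- Schoenfeld: 0.3567 × 12.61/2 - 1.96 = 0.288, power 61%
- Freedman: 0.1765 × 12.61 - 1.96 = 0.265, power 60%
- Lakatos: 60.6%, and all nine cells within 1.6 points of print

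Uniform follow-up on 21 to 42 months (Lakatos) gives 59.4% and matches all nine cells within 0.6 point. The same set-up reproduces the cardiovascular Table 3.3.4 within 0.5 point. Cardiovascular events are ascertained every six months throughout, so full follow-up suits that table.

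**Step 2: who is last seen when.** Under uniform recruitment, (30 - 23)/19 = 7/19 = 37% are followed for less than 30 months and 12/19 = 63% reach month 30. Section 10.2.1 allows four weeks on each side of a visit. If the month-30 visit can take place from month 29, the month-18 group is 6/19 = 32%. Under the accelerated recruitment scenario it is about 43%. Mean observable time before losses is 12/19 × 2.5 + 7/19 × 1.5 = 2.13 years, against 32.5 months = 2.71 years for full follow-up.

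**Step 3: the quoted cell on the actual schedule.**

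| | To 30 months | To 18 months | Weighted 12/19, 7/19 |
|---|---|---|---|
| Control | 0.1089 | 0.0697 | 0.0944 |
| Intervention | 0.0776 | 0.0493 | 0.0672 |

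D = 800 × 0.1616 = 129.
- Schoenfeld: 0.3567 × 11.37/2 - 1.96 = 0.068, power 53%
- Freedman: 0.1765 × 11.37 - 1.96 = 0.047, power 52%
- Lakatos: 52.0%

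Reading the 5% directly as a hazard gives 51-52%. Using the 32% share gives 53-54%. Counting an event only if the detecting visit is attended gives about 51%.

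**Step 4: all nine cells** (Lakatos, 37% share), recomputed with the printed figure in brackets:

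| Effect | 3%/yr | 5%/yr | 7%/yr |
|---|---|---|---|
| 20% | 17 (20) | 25 (30) | 33 (39) |
| 30% | 35 (40) | 52 (59) | 66 (73) |
| 40% | 58 (66) | 79 (86) | 90 (95) |

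The gaps run from 2.9 to 8.5 points. Schoenfeld gives 2.8 to 6.8. With the 32% share the gaps are 2.6 to 7.5 (Lakatos) or 2.5 to 5.8 (Schoenfeld). With rates read as hazards the largest gap is about 9.

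**Step 5: where the loss comes from.** Ending observation at month 30, but otherwise following everyone to the end of their time, costs only about 1 to 5 points. The rest comes from the participants last assessed at month 18.

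**The case against.** Section 3.3 does not state the observation period behind Table 3.3.7, so it is inferred from fit, and the fit is not unique. A reader might infer that only the full 23 to 42 months can produce the table. The figures do not support that: a flat 31 months fits within 1.0 point (Lakatos), and 30 months for everyone fits within 1.3 (Schoenfeld, 58.6-58.7% in the quoted cell). A planner may have used 30 months because the last instrument falls there. This stands against any claim of uniqueness, but it does not rescue the table, because a minimum follow-up of 23 months rules out 30 months for all.

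A reader might also infer that the stop at month 30 is the main fault. It is not: Step 5 shows that it is the smaller part.

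The replacement figures are conditional too. They keep all 1,600 at risk, although the endpoint is a first disturbance and Section 3.3 makes a 10% baseline-prevalence allowance for cognitive impairment but none here. As an illustration only, 10-20% prevalence at baseline would bring the quoted cell to about 48-44%, while the permitted maximum of 1,680 participants would raise it to about 54%. This is fair, and it is a reason to state the assumptions beside the number.

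Finally, the outcome is exploratory, the printed power is already modest, and moving from 5% to 3% per year in the same row costs 19 points (59% to 40%). That limits the weight of the point. It does not make the printed figure consistent with the visit table.

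**Conclusion.** The point holds. The protocol prints a power that its own assessment schedule does not deliver. In the 5%/yr, hazard ratio 0.7 cell, power is about 51-54% rather than 59%, with about 129 expected events rather than 155 to 159. All nine cells are too high, by about 3 to 8 points depending on the log-rank formula and the visit window, and by up to about 9 if rates are read as hazards. The main cause is the third or so of participants (32-37% under uniform recruitment) whose last sleep-wake assessment is at month 18.

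This rests on exponential event and loss times, 800 per arm, uniform recruitment, and no sleep assessment outside the printed schedule. The accelerated recruitment scenario would lower power slightly further. A reader might infer that the size of the trial or the primary analysis is affected. The documents give no support for that: this is a tertiary aim, and the sample size rests on major mobility disability.

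**What to change.** Recompute Table 3.3.7 and the sentence in Section 3.3 with observation ending at each participant's last scheduled sleep-wake assessment: month 30 if planned follow-up reaches it, otherwise month 18. Replace 59% with about 52% and revise the other eight cells to match, along the lines of the Step 4 table. State beside the table the observation period assumed, the share of participants taken as last assessed at month 18, and whether participants with a disturbance at baseline are counted as at risk.

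The cost is one recalculated table and a sentence or two of protocol text. Visits, sample size and the analysis model stay as they are. The stated power becomes less favourable.

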#### **4. Study Population**

The eligibility criteria for the LIFE Study identify participants who are not currently disabled but have moderate to high risk for occurrence of mobility disability and for whom the intervention is safe.

The Coordinating Center monitors the distribution of the recruited cohort with respect to age, gender, ethnicity, score on the Short Physical Performance Battery (SPPB) and other factors expected to influence the incidence rate of the trial's primary outcome. Based on this monitoring activity, targeted recruitment strategies are developed to ensure that the study cohort is racially and ethnically diverse and has a range of age and physical performance adequate to evaluate the results of this study.

#### **4.1. Eligibility Criteria**

##### **4.1.1. Targeting Populations at High Risk of Disability**

Targeting the non-disabled but high-risk segment of the older population for a physical activity program aimed at reducing disability has many advantages. These persons are in the middle of the functional spectrum and are neither so disabled that a physical activity program may not offer help nor so highly functional that their already very low risk of becoming disabled would not be appreciably affected by the intervention. They may be at a transitional stage in the pathway to disability, so that a well-focused intervention could be extremely effective in pulling them back from the brink of disability onset and lead to additional years of disability-free life.

Most of the older population is non-disabled and an important goal in this segment of the population is to prevent or postpone the onset of disability. However, there is a great deal of heterogeneity in the non-disabled portion of the older population and any strategy to prevent disability should take the very broad range of health status into account. Some older non-disabled persons are already very active and vigorous while others are sedentary and may actually have impairments and functional limitations that indicate an elevated risk of disability. The eligibility criteria in this study are aimed at identifying persons who are sedentary, have functional limitations, as assessed by a battery of physical performance tests, but who have not yet developed disability, as documented by their ability to walk 400 meters without sitting or the help of another person. Targeting this subset of the population makes it possible to recruit a non-disabled but at risk population for a clinical trial of disability prevention. In addition, evaluating the role of physical activity in preventing the onset of mild cognitive impairment and Alzheimer's disease is an important secondary aim of the LIFE Study so its cohort will also be selected to be free of significant cognitive impairment. This is a large segment of the older population in which successful prevention of disability onset, in this case through a physical activity program, would have a major public health impact.

##### **4.1.2. Establishing Eligibility**

Eligibility is established in a multi-step screening process. The first step is a telephone screen to assess specific inclusion and exclusion criteria. This is followed by an interviewer assessment, including the administration of the SPPB, the 400 meter walk test, the Modified Mini-Mental State (3MSE) exam and an interview. Finally, the potential participant receives an examination by the study physician, physician assistant or nurse practitioner, who determines if conditions are present that meet exclusion criteria. Eligibility criteria are as follows:

**Gender** Men and women are eligible. The LIFE Study endeavors to recruit men and women in rough proportion to their representation in the catchment area population.

**Age** Individuals aged 70-<90 years old are eligible. This age group is selected because it is at high risk of major mobility disability, and it may have a sufficiently long life expectancy to participate in a full-scale RCT, which would have a duration of 3 to 4 years.

**Ethnicity** All ethnic groups are eligible for the study. The LIFE Study goal is for a study cohort that is at least 22.5% from minority populations (primarily African Americans and Hispanic Americans).

**Residency** Participants must be planning to reside in the area for at least 2 years.

**Functional Status** Summary score <10 on the Short Physical Performance Battery (SPPB). Ability to complete the 400 m walk test within 15 minutes without sitting or the help of another person, or the use of a walker. The LIFE Study goal is a target of 45% of randomized participants to have a score of < 8.

**Cognitive functioning** Persons are eligible if they do not report a diagnosis of dementia or score lower than our education-based cut-points on the Modified Mini-Mental State Exam (3MSE). Persons with 9 or more years of education who score <80 (<76 if African American) and those with less than 9 years of education who score <76 (<70 if African American or Spanish speaking) are excluded. Persons excluded because of low 3MSE scores will be advised by the research staff to take the results to his/her PCP for additional review since our testing is for research purposes only.

**Physical activity and exercise** Sedentary lifestyle is operationally defined as spending less than 20 minutes per week in the past month getting regular physical activity. Physical activity includes activities like: brisk walking, jogging, weight lifting, cycling, aerobics, and dancing. In addition, reports less than 125 min/week of moderate physical activity based on the modified 18-item CHAMPS questionnaire.

**Chronic disease status** The LIFE Study recruits individuals both with and without chronic diseases, except for specific conditions described in the exclusion section that may be life-shortening or prevent the participation in a physical activity intervention.

**Willingness to participate** Participants must be willing to give informed consent, be willing to be randomized to either Physical Activity or the Successful Aging Program intervention, and to follow the protocol for the group to which they have been assigned.

